#### Generating Information Items

The first step in the Delphi process involves generating a list of information items for the voting consensus process. The procedure comprises 3 steps, described in the following sections.

##### Scoping Literature Review and Patient Interviews

In structuring the Delphi procedure, we sought to cover the wide spectrum of DCM-related information with the potential to foster patient understanding of the condition, facilitate informed decision-making, and promote efficient self-management. Clinically pertinent items were derived from scientific publications, patient leaflets, health websites, and videos identified in a scoping review of DCM education resources [38]. In total, 150 information resources were reviewed, spanning 115 (76.7%) scientific publications, 28 (18.7%) videos, and 7 (4.7%) health organization resources and health education websites. Items sourced in this manner characterized the disease etiology, pathophysiology, epidemiology, management, and outcome prediction. Additional multidimensionality was added via items sourced from qualitative research involving patient focus groups [10,113] and semistructured interviews [45]. These provided valuable additions focused on the impact of DCM on employment, mental health, and quality of life. The process of deriving the information items was iterative. Each new unique piece of information was noted as an item, and multiple returns to the data were made to ensure the avoidance of duplicates and omissions. This process continued until a preliminary list of information items (n=95) was collated and no new items could be identified.

##### Professionals’ Perspectives

Professionals’ views on the information items to be included in the diagnosis CIS were identified using an open-ended qualitative questionnaire (SurveyMonkey; Momentive Inc). Respondents were provided with relevant information via a web hyperlink to the Participant Information Sheet. The sheet included a summary of the research project, its objectives, the inclusion and exclusion criteria, anonymity and confidentiality, and the anticipated time commitment required to complete the survey. To stimulate participant engagement, a short educational video explaining the purpose of the procedure was presented [114]. Biographical information, including training specialty (surgery or other HCP), was collected from consenting participants. Respondents were subsequently directed to a page containing the following open-ended question: “What information do you think people with DCM need to be told at the point of diagnosis about their condition?” It is acknowledged that free-text questions do not generate rich qualitative data [115]. However, our objective was not to elicit robust qualitative insights but rather to generate a list of information items from the professionals’ perspectives. To mitigate this limitation, participants were asked to provide a short rationale for each recommended information item. This approach can act as a proxy for qualitative interviews administered to convenience samples [116] and allowed the study team to improve evaluative rigor by understanding the rationale behind the recommendations received. There was no limit on the number of information items that the HCPs could submit.

To facilitate reflective consideration from respondents, participants were presented with a word cloud upon submitting their initial recommendations (Multimedia Appendix 1). Word clouds are a graphic representation of textual data that use frequency counts to display effective summaries of common themes within a given text [117] and have been successfully used previously in DCM consensus work [118,119]. The word cloud generated for this study was produced using qualitative codes derived from the thematic analysis of interviews with people with DCM on the topic of their information needs [45]. This approach was selected to mitigate issues related to language variability that can arise from using direct quotes from the participants, which may be influenced by individual differences in language proficiency, education, and cultural background, and to improve the comprehensibility of the word cloud. Similar adjusted approaches have been used by others [117]. Participants were asked to reconsider their recommendations after viewing the word cloud. As word clouds have been found to promote critical thinking and reflection [120], we hypothesized that this approach would help stimulate professional stakeholders to generate insightful recommendations that are better aligned with patients’ needs. The open-ended questionnaire was not issued to people with DCM as their perspectives have already been collected [45].

##### The Questionnaire

A total of 46 respondents, predominantly spinal surgeons (n=33, 72%), suggested information items (n=312) for inclusion in the Delphi survey. Contributors also included physiotherapists (8/46, 17%) and other HCPs, including neurologists, family physicians, allied health professionals, and researchers (5/46, 11%). The items received were carefully scrutinized for redundancy. On inspection, suggestions paralleled our existing list, demonstrating a broad alignment across all information sources, including the expert clinician group. A multidisciplinary study committee comprising 3 people with DCM, 3 neurosurgeons, a neurologist, 2 consultant physiotherapists, a lay representative, and the study coresearcher condensed the list to 31 information items and classified them into 8 distinct categories deemed to accurately represent their content. For the purposes of developing a CIS, the term “information item” was conceptualized as overarching categories or topics that house more specific, detailed information. For example, the item “lifestyle factors” was an inclusive banner for detailed subjects such as the effects of smoking and occupational trauma on DCM. This approach was chosen to ensure the appraisal of *meaningful* concepts or core educational aspects. The detailed content within each item, although not voted upon, will be accessible for participants’ reference throughout the Delphi study. Categorizing information items in Delphi studies is crucial in reducing redundancy and ensuring that all relevant concepts are captured as well as promoting consensus building among expert panelists by clarifying the meaning of each item [79,80]. This also facilitates a systematic and standardized approach to synthesizing diverse perspectives, thereby generating informed recommendations [79,121]. In preparation for pilot-testing, the research team created a draft survey based on the final list and evaluated the software settings, automation, flow, ease of navigation, and completion time. For ease of navigation, only 1 information item was presented per page [122].

#### Pilot Survey

Pilot-testing was conducted with the study committee. Feedback concerning the language, structure, readability, comprehension of statements, and formatting of the questionnaire was collected through open- and closed-ended questions.

#### Delphi Survey

An email campaign will be created in Gmail (Google) using a newsletter layout template and sent to HCPs, people with DCM, and carers in the contact directory of the RECODE-DCM network using the multisend function. The multisend option is a built-in mass-email feature that allows emails to be sent in bulk to distinct recipients, thus preserving their anonymity, which is a key feature of the Delphi method [98]. Participants will have the option to opt out of the process at any point through a unique “unsubscribe” link automatically added to each email. Recipients who unsubscribe will be removed from future email campaigns. The email will provide prospective Delphi panelists with a brief overview of the study. Potential panelists will be directed to Delphi round 1 via a SurveyMonkey web link embedded in a participation button at the bottom of the email. The survey will open to a short explanatory video and a web link to the Participant Information Sheet, which will provide a summary of the research project, aims, the inclusion and exclusion criteria, anonymity and confidentiality, and anticipated time commitment. The following biographical data will be collected for people with DCM: age, year of diagnosis, history of surgery or nonoperative management, and employment status. For HCPs, information about their profession, specialty, job title, and experience in managing DCM will be captured.

Panelists will be asked to independently rate the importance of information items using a 4-point Likert scale (“essential,” “very important,” “unimportant,” and “not at all important”). This range of response categories is more likely to produce stable findings in Delphi studies [95]. Respondents will also be asked to provide a brief rationale for their responses and whether the information items presented could be modified to improve their relevance using a comment box. It is common practice to include in questionnaires that respondents themselves complete an invitation to add issues not covered in the main part of the questionnaire or to expand on terms [123]. The presentation of information items will be randomized using a pseudorandom number generator throughout both rounds [124]. No more than 3 rounds will take place to ensure that the process does not become too repetitive and time-consuming to maintain an adequate response rate [80]. After each round, participants will be asked to read the feedback before responding again to statements.

#### Data Analysis

##### Overview

Qualitative and quantitative summaries will be used to understand areas of agreement or disagreement between panelists, generate feedback, and stimulate participants’ reflections. All forthcoming data analyses will be carried out by a postgraduate research assistant. Both quantitative and qualitative methods will be used to analyze interround feedback, and the findings will be reported to the panelists and the core research team after each round. The provision of both types of data is essential to enhance rating accuracy [125].

##### Qualitative Analysis

Free-text comments will be analyzed using inductive content analysis [126], a procedure commonly used with text-based data. Its pragmatic emphasis on theoretical constructs makes this approach particularly suited to practically oriented research where the goal is to describe a phenomenon of interest [127] and generate answers for the application of findings [128]. A summary of the remarks made by other panelists will be displayed anonymously to participants after each round.

##### Descriptive Statistics

Following each round, panelists will receive aggregate-level summary statistics for each item in the form of frequency percentages, medians, ranges, and IQRs [129]. Participation and attrition rates will be summarized as frequencies and percentages after round 2. Participants will be asked to read the summarized feedback before responding to round 2 statements.

##### Interrater Stability

Descriptive statistics reflect the level of overall consensus in a given sample but may not account for random change agreement and, therefore, may fail to accurately depict “true” consensus [130]. The κ statistic measures agreement beyond that expected by chance [130]. A weighted κ coefficient will be calculated after round 2 for the between-participant agreement on each information item. This variant is preferred compared with its unweighted equivalent as it is more suited to ordinal data given its ability to account for the magnitude of differences between the agreement levels [131]. The κ statistic will be particularly helpful for guiding the direction of conversations during the consensus meeting, ensuring that discussions are rooted in objective findings. κ calculations will be provided for each information item along with the reference value description of the agreement level in accordance with the study by McHugh [132] (Table 2).

No information items will be removed during these rounds. Data analyses will be conducted using SPSS (version 26; IBM Corp), and graphs will be produced using Microsoft Excel (Microsoft Corp).

**Table 2 table2:** Level of agreement represented by κ values^a^.

κ value	Agreement level
0.0-0.2	None
0.21-0.39	Minimal
0.40-0.59	Weak
0.60-0.79	Moderate
0.80-0.90	Strong
≥0.90	Almost perfect

^a^Adapted from the study by McHugh [132].

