#### Sample Size

The optimal participant head count for a Delphi study remains a subject of ongoing discussion [82], as exemplified by the historical variance in sample sizes [95]. However, representativeness is not shaped by conventional sampling strategies [96,97] but rather through the expertise of the panel members [98]. Guidelines suggest a minimum of 7 to 15 panelists for optimal reliability [78]. Some believe that exceeding 30 participants adds little value [99-101]. To develop a relevant CIS, our study aims to target the 2 primary DCM stakeholders: people with DCM and HCPs managing DCM. We propose enlisting at least 15 experts from each category, with no upper limit [78,95,102]. We address potential carer involvement in the following section.

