For balanced geographical stakeholder representation, a 1:1:1 target ratio is proposed, spanning North America and Australasia; Europe and the United Kingdom; and “elsewhere,” comprising Africa and Asia. Including stakeholders from these regions will help ensure that the CIS considers a wide range of health care systems, cultural practices, and resource availability. However, it is worth noting that engaging participants from the “elsewhere” category may prove difficult. These regions, which are often underrepresented in the research community owing to fewer research resources and infrastructure [110], are similarly underrepresented in our specialized RECODE-DCM community. Recognizing this potential recruitment challenge upfront, we will aim to achieve equal regional representation during the final consensus meeting, with no items removed before this stage.

Carers (informal and formal) of people with DCM will also be invited to participate in the Delphi process as they offer significant practical and emotional support to people with DCM [16] and likely hold unique perspectives with regard to their information needs at the time of diagnosis. Consultation with informal carers, often subject to significant caregiving strain [16], may indirectly contribute to their welfare by promoting improved standards of care. However, we acknowledge that the recruitment of carers may be challenging as they are less likely to self-identify, as documented in related research domains [111]. In addition, the number of carers involved in the RECODE-DCM community is currently limited. For these reasons, no stakeholder or geographical target ratios will be specified for this group. Their involvement will be encouraged by existing HCPs and people with DCM in the community.

Participants will be invited to complete round 2 of the Delphi survey only if they have responded to round 1. A dropout rate of approximately 20% is expected from previous Delphi exercises [95,112]. Respondents who complete the Delphi process will be acknowledged in published material. No monetary incentives will be offered.

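### A weighted κ between participants, computed separately for each information item, does not depend on how the panel voted, so it cannot show agreement or guide the meeting

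*Protocol article*

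**What the plan says.** The interrater stability section justifies κ by noting that descriptive summaries may not allow for chance agreement: "The κ statistic measures agreement beyond that expected by chance". It then fixes the statistic, its unit and its timing: "A weighted κ coefficient will be calculated after round 2 for the between-participant agreement on each information item". It fixes the labelling too: "κ calculations will be provided for each information item along with the reference value description of the agreement level", with the bands in Table 2, the lowest of which is 0.0–0.2 ('None'). It also states a purpose: "The κ statistic will be particularly helpful for guiding the direction of conversations during the consensus meeting".

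Three other places settle what data enter each κ.
- The Delphi survey section gives one rating per panelist per item per round: "Panelists will be asked to independently rate the importance of information items using a 4-point Likert scale".
- The questionnaire section says the study committee "condensed the list to 31 information items", and that the detailed content inside an item is shown for reference but not voted on.
- The sample size section sets the panel: "We propose enlisting at least 15 experts from each category, with no upper limit". There are two categories, people with DCM and health care professionals.

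The article names no multi-rater version of κ, no weights, no fixed chance reference and no pooling over items. The section heading speaks of stability, but the text describes agreement between participants after round 2, not agreement between rounds.

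**The concern.** κ compares observed agreement with the agreement expected by chance. The usual forms estimate chance from how often raters use each category across many rated objects. Here each κ has only one object, the single item, rated once by each panelist. The votes that give the observed agreement also give the chance agreement, and nothing else informs either term.

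At stake is whether the added statistic does the job given to it. It is brought in because percentages alone might misrepresent true consensus, and it is to help direct the consensus meeting, where the final vote is taken. If its value is the same for a nearly unanimous item and an evenly split one, it does neither, and each item carries a number and possibly a label unrelated to the panel's views.

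**Working it through.** The article states no κ value, so there is no figure to reproduce. The check is algebraic, followed by numbers.

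**Inputs.** Four ordered categories (Delphi survey). One rating per panelist per item (Delphi survey, questionnaire). Panel of at least 15 + 15 = 30 (sample size). With "A dropout rate of approximately 20% is expected from previous Delphi exercises" (expert selection), about 30 × 0.8 = 24 remain at round 2. There are 31 items (questionnaire). Weights are not stated, so unweighted, linear and quadratic are all tried.

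**Fleiss-type κ, one item.** Let c_j be the number of votes in category j, n the number of panelists, p_j = c_j/n, and d_jk the disagreement weight, with d_jj = 0.
- Observed pairwise disagreement: Do = Σ c_j c_k d_jk / [n(n−1)].
- Chance disagreement: De = Σ p_j p_k d_jk = Σ c_j c_k d_jk / n².
- Ratio: Do/De = n/(n−1), whatever the c_j and d_jk, provided De > 0.
- Hence κ = 1 − Do/De = −1/(n−1).

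The votes and the weights cancel. If all votes agree, Do = De = 0 and κ is 0/0.

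**Pairwise Cohen/Conger κ, one item.** Each rater's marginal distribution is that rater's single vote, so for every pair the expected agreement equals the observed agreement. Averaged over pairs, Po = Pe and κ = 0, or 0/0 if the item is unanimous.

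**Numbers at n = 30, linear weights** (votes in scale order from 'essential'; top two = the two favourable categories):

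| Votes | Top two | Do | De | Fleiss-type κ | Pairwise κ |
|---|---|---|---|---|---|
| 29/1/0/0 | 100% | 0.0222 | 0.0215 | −0.0345 | 0 |
| 20/8/2/0 | 93% | 0.1962 | 0.1896 | −0.0345 | 0 |
| 8/8/7/7 | 53% | 0.4299 | 0.4156 | −0.0345 | 0 |
| 15/0/0/15 | 50% | 0.5172 | 0.5000 | −0.0345 | 0 |
| 30/0/0/0 | 100% | 0 | 0 | undefined | undefined |

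First row by hand: Do = (29 × 1/3)/435 = 0.0222, where 435 = 30 × 29/2 pairs. De = 2 × (29/30) × (1/30) × 1/3 = 0.0215. The ratio is 30/29, so κ = −1/29 = −0.0345. Unweighted and quadratic versions give the same κ in every row. Over 5000 random vote patterns with n from 5 to 99, the largest departure from −1/(n−1) among non-unanimous patterns was 1.5 × 10⁻¹⁴.

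**Dependence on panel size alone.** n = 15: −0.071; n = 24: −0.043; n = 30: −0.034; n = 60: −0.017.

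**What does vary with the votes.** A coefficient with a fixed uniform chance reference (Brennan–Prediger type) uses 1 − Do/Du, where Du = 20/(3 × 16) = 0.4167 for linear weights on four categories. The five rows above give 0.95, 0.53, −0.03, −0.24 and 1.00.

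**The case against.** The strongest reply is that κ decides nothing. Items enter or leave by the ≥75% rule, applied after the consensus meeting, and none is removed in rounds 1 and 2. The one trigger for guided discussion and a repeat vote at the meeting is a 50% split in live percentages. Panelists also receive percentages, medians, ranges and IQRs for each item. All of this stands, and it limits the harm to an uninformative column beside informative ones.

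A second reply is that the article names no estimator, so a workable one could still be chosen. This stands in part. A fixed-chance coefficient per item would vary with the votes, so it would be too strong to infer that no chance-corrected index per item is possible. But the article calls for a weighted κ and mentions no such reference. Other readings do not repair the text: content within items is not voted on, the unit is given twice as each item, and the agreement described is between participants rather than between rounds.

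A reader might also infer that every item would be labelled 'None' and panelists told that nobody agrees on anything. The documents do not support that. Only a value of 0 falls in the 'None' band; a negative value has no band, a unanimous item has no value, and the percentages would show the actual agreement.

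**Conclusion.** The point holds for any standard κ whose chance term comes from the observed votes. Computed per item, as the article specifies, it is −1/(n−1) or 0 for each non-unanimous item and undefined for each unanimous one. This applies to all 31 items and does not depend on the weights. The statement is wrong as written rather than a detail left to a fuller document, because an analysis plan that followed the stated statistic and unit would inherit the defect.

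The result rests on two assumptions: each panelist contributes one vote per item, which the article supports, and the estimator is of the Fleiss or Cohen/Conger type, which is the natural reading but is not stated.

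This is a should-fix. It would go too far to infer that the core information set itself is compromised: the set can be produced by its stated rule without κ.

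**What to change.** Reword the κ paragraph. Drop the per-item κ between participants and its Table 2 label, and let the percentages and IQRs already planned for each item guide the discussion.

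If a chance-corrected measure is wanted, name one that can be computed:
- One multi-rater weighted κ across all 31 items, overall and by stakeholder group, with weights stated and Table 2 labels kept. It measures whether panelists separate items alike, so it can be near zero when all items are rated similarly. In a simulation with 30 raters it was 0.00–0.01 when every item shared one vote distribution (90% expected in the top two categories), and 0.21–0.23 when distributions varied.
- A weighted coefficient per item with a fixed uniform chance reference, without the Table 2 labels, which were not set for it.
- A within-person weighted κ per item between rounds 1 and 2, which would match the section heading. This is possible only if responses can be linked by a pseudonymous code. The surveys are described as anonymized, and knowing who answered round 1 does not by itself link the votes.

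The first two options use data already planned and cost a change of wording. The third may need an identifier that the article does not describe. The downside is that the per-item κ column is lost or replaced by a differently defined index.
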